### Blinding

Researchers assessing secondary outcomes are blinded to intervention/control status of schools, but those who are visiting schools to collect fidelity measures and provide top-up intervention training are not blinded. Schools were informed of their status following baseline measurements, so that intervention school teachers could receive training and deliver the intervention.

### Outcome measures

#### Primary outcome measure

The primary outcome measure is academic attainment, assessed by the Progress Test in Maths (PTM), Level 13 [38]. To reduce the test burden, NatCen will administer the test to a random selection of half of all form groups per school, post-intervention only [37].

#### Secondary outcome measures

##### Cardiorespiratory fitness

Fitness is being assessed using the 20-m multistage shuttle run test [39]. This well-validated test [40] measures participants’ maximum aerobic capacity. Schools with a policy of not using the multistage fitness test are completing the Cooper Run Test [41], which requires pupils to run or walk as far as possible in 12 min around a measured track (between 80 and 400 m). Fitness measures are being collected once at baseline and once during the summer term. The tests are conducted by PE teachers during regular PE lessons to minimise the burden on participants and to avoid disrupting other classes.

##### Cognitive and mental health assessments

Cognitive and mental health measures are being collected once at baseline and once during the summer term at the end of the intervention. All cognitive assessments and health questionnaires have been programmed in JavaScript using jsPsych [42], a JavaScript library for running behavioural experiments in a web browser that allows for accurate response time measurements [43]. Only participants can access the assessments, using a personal ID number. Once the assessments are completed, summary measures are created and temporarily stored against participants’ personal IDs in a secure database before being transferred to a second, secure research database, against private ID numbers to ensure anonymisation.

##### (a) Cognitive measures

Cognitive performance is being assessed with tests of processing speed, visual relational memory and core executive functions (working memory, inhibition and cognitive flexibility) [44] that are well validated in children and have been shown to be sensitive to the effects of PA [11, 45]. The cognitive battery takes approximately 50 min to complete and comprises the following tasks:Processing speed is assessed using a simple reaction time task.Visual relational memory performance is assessed with a modified version of a previously described paradigm [10].Inhibitory control is assessed with a modified version of the flanker task [46].Working memory is assessed using a modified version of the visual 2-back task [47, 48].Cognitive flexibility is assessed using a modified version of the colour-shape switch task [46].

Details of each task are provided in Additional file 2.

The task order is pseudo-randomised across participants within schools: all participants start with the reaction time task (i.e. processing speed), followed by the remaining four tasks in a random order (see Additional file 2 for details on the randomisation process). Teachers were instructed to ask pupils to complete the tasks at home, as pilot tests in three schools indicated that the local IT environment (e.g. bandwidth) may not be able to cope with large groups of pupils (> 20) completing the tasks at the same time, and it was deemed a logistical burden on schools to set the tasks during school lessons. Nevertheless, some schools have decided to complete the tasks during school time, as they felt this was easier to manage.

##### (b) Mental and physical health measures

The mental and physical health questionnaire takes approximately 20 min to complete and is intentionally kept brief so that it can be easily completed in school. The questionnaire comprises the following core measures:*Mental health* is assessed with the Strengths and Difficulties Questionnaire (SDQ) [49].*Global self-esteem* is measured using the global self-esteem scale of the short version of the Physical Self-Description Questionnaire (P-SDQ) [50].*Physical self-esteem* is measured using the physical self-esteem scale of the short version of the P-SDQ [50].*Global health* is measured using a single item on a 5-point scale drawn from the Health Behaviour in School-Aged Children (HBSC) survey [24]: ‘In general, how would you say your health is?’ (5 = excellent to 1 = poor).*Physical activity* is measured with a single item [51]: ’In the past week, on how many days have you done a total of 60 minutes or more of physical activity, which was enough to raise your breathing rate? This may include sport, exercise, and brisk walking or cycling for fun, or to get to and from places’.*Habitual physical activity over the past 6 months* is measured with a single item drawn from previous studies [52]: ’Thinking about the past six months, how often have you been physically active for an hour every day during a typical week in school term?’ (1 = never to 7 = always).

We additionally explore the effect of the intervention on daytime sleepiness, PE enjoyment and psychological variables linked to daily MVPA.7.*Daytime sleepiness.* During adolescence the circadian system delays and lengthens, causing sleep timing to shift later [53], which can lead to daytime sleepiness [54] and behavioural issues including school lateness, absenteeism and, ultimately, poor academic performance [55–57]. Based on evidence of a positive relationship between VPA and sleep quality and quantity in young adults [58] and suggestions that exercise programmes might improve aspects of adolescent sleep [59, 60], the study will investigate the intervention’s impact on daytime sleepiness using the Paediatric Daytime Sleepiness Scale (PDSS) [61].8.*PE enjoyment.* To investigate the acceptability of the intervention with Year 8 pupils, we measure PE enjoyment with a single item [62]: ’I enjoy PE.’ (1 = strongly disagree to 7 = strongly agree).9.*Psychological variables linked with daily MVPA.* Understanding the extent to which a programme of VPA during PE might impact psychological variables with potential to explain variance in overall daily MVPA is important, given the low adolescent activity levels [24]. We use the Theory of Planned Behaviour [63, 64] and the Prototype Willingness Model [65] to investigate whether the intervention changes attitudes and beliefs about daily MVPA and active types of people. All items relating to constructs from the Theory of Planned Behaviour and the Prototype Willingness Model were developed according to established theoretical [63, 64] and practical [66, 67] guidelines. An overview of the measures is provided in Additional file 2.

##### Physical activity during PE

Objective measures of VPA during PE are being collected in each school once during regular lessons at baseline (May–July 2017, and at some remaining schools in September 2017) and again during lessons in spring term (March–May 2018). Each school is visited at each timepoint to test at least 50% of the pupils in the year group. Measures are taken using the Axivity AX3, a wrist-worn tri-axial accelerometer designed by Open Lab, Newcastle University, UK. Trained research assistants show pupils how to fit the AX3 on their non-dominant wrist. The devices are attached after pupils change for PE and collected before they change back into school clothes. Class average minutes of MPA and VPA during active lesson time are calculated using established cut-points [68] and standardised, for comparison purposes, to minutes per hour.

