### Randomisation

Schools (*n* = 104) were randomised into an intervention group or control ‘PE as usual’ control group using stratified block randomisation and an allocation ratio of 1:1 (Fig. 2). Stratification was arranged by single-sex/co-educational status of schools. NatCen performed the randomisation using a random number generator in STATA (v.12) [36, 37]. To reduce the risk of bias, schools were informed of their assigned group by the research team after completing baseline assessments.

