### Intervention

The intervention consisted of a one academic year (10 months: September 2017–June 2018) PA programme delivered by PE teachers during regular Year 8 PE lessons. In the summer term prior to the trial, Year 8 PE staff from all intervention schools were invited to attend a 2-h face-to-face training session delivered by a team from Oxford Brookes University who designed the intervention. Those unable to attend were asked to join an interactive 2-h online training session delivering the same content. Teachers unable to take part during the summer term attended training at the start of the autumn term. During these sessions, the intervention was described to the teachers.

The intervention requires teachers to deliver specific elements of additional VPA, over and above normal VPA, during all Year 8 PE lessons, for the whole school year. Four minutes of VPA are incorporated into the PE lesson as part of a warm-up, and three 2-min infusions per hour of PE are incorporated into the main PE class. In this study, VPA is defined as activities that raise the heart rate (HR) to 71–85% of the maximum HR (HRmax), whereas moderate PA raises it to 60–70% of HRmax. The intervention elements are designed to be easy to incorporate into PE lessons, to maximise the training effect and to minimise the risk of injury with a warm-up that progresses from light to moderate-intensity activities and includes bursts of VPA.

Teachers were asked to deliver an active 10-min warm-up at the start of each lesson, beginning with light-intensity movements (e.g. wrist rotations; leg swings) and moving through moderate-intensity activity (e.g. arm rotations; walking with high knee-raise) to incorporate two periods of VPA (e.g. vigorous arm sprints; running on the spot) totalling 4 min. Fifteen young adolescents piloted the warm-up and the infusions while wearing chest strap Polar heart rate monitors, which indicated that heart rates were in the vigorous zone for the specified time during all the intervention elements.

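### The September 2017 accelerometer readings counted as baseline are not assured to precede disclosure of the arm or the start of the intervention

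*Protocol article*

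**What the plan says.** The section on physical activity during PE schedules the first accelerometer visit "at baseline (May–July 2017, and at some remaining schools in September 2017" and the second in March–May 2018. Both take place in regular lessons.

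The Intervention section gives the programme's dates: "The intervention consisted of a one academic year (10 months: September 2017–June 2018) PA programme". The extra activity is due "during all Year 8 PE lessons, for the whole school year", and no run-in is described. On training it says: "In the summer term prior to the trial, Year 8 PE staff from all intervention schools were invited to attend". It adds: "Teachers unable to take part during the summer term attended training at the start of the autumn term". Control schools received no training.

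On disclosure, the Randomisation section says that, to reduce the risk of bias, "schools were informed of their assigned group by the research team after completing baseline assessments". The note to Fig. 2 says the same, and the Blinding section says: "Schools were informed of their status following baseline measurements, so that intervention school teachers could receive training and deliver the intervention".

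The Design section places baseline at the end of Year 7. The recruitment section has the same pupils in Year 8 when the intervention starts, in academic year 2017–2018.

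**The concern.** A baseline serves as a baseline only if treatment, and knowledge of treatment, cannot have affected it. The article states that protection for all baseline assessments, yet for one outcome it allows a measurement window that runs into the treatment period.

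VPA during PE is part of the second hypothesis. It is also the objective measure of delivery listed under Intervention fidelity; the others are teacher logs and a three-item pupil survey. If an intervention school's September lesson already contained the extra activity, its baseline would be raised. Any analysis that subtracts or adjusts for that value would then remove part of the effect, in the intervention arm only. If staff merely knew their arm, they could still have run the observed lesson differently.

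**Working it through.** The article gives no figure to reproduce. The first check is of dates; the second shows what size of bias could follow.

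**Dates side by side, for an intervention school visited in September 2017**

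| Statement | Section | Does the September visit fit? |
|---|---|---|
| Baseline is the end of Year 7 | Design | No; pupils are in Year 8 |
| Intervention runs September 2017 to June 2018, in every Year 8 PE lesson | Intervention | The visit falls in the first month of that period |
| All intervention schools invited to training in the preceding summer term | Intervention | The visit comes after the invitation |
| Arm disclosed only after baseline was complete | Randomisation, Fig. 2 note, Blinding | Not if the invitation came first, since only intervention schools were trained |

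There are three ways to ease the conflict:

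1. Disclosure was held back for late schools. The statement that all intervention schools were invited in the summer term is then too broad.
2. The visit came before the first intervention lesson. This is possible, particularly where teachers trained only in the autumn, but nothing in the text assures it, and the summer invitation would still have come first.
3. Only control schools were visited in September. Contamination is then absent, but baseline falls in different terms and school years in the two arms.

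Each of these needs a correction or a disclosure.

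**Size if the readings are used as baseline**

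Notation:
- δ is the true effect on VPA, in minutes per hour.
- q is the share of intervention schools whose baseline already contains the full effect.
- b is the weight on baseline: 1 for a change score, the regression slope for a covariate, 0 if baseline is not used.

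Contamination raises the intervention arm's mean baseline by q×δ. The estimate then has expectation δ − b×q×δ, so the relative shrinkage is b×q.

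| q | b = 0 | b = 0.5 | b = 0.7 | b = 1 |
|---|---|---|---|---|
| 10% | 0% | 5% | 7% | 10% |
| 20% | 0% | 10% | 14% | 20% |
| 30% | 0% | 15% | 21% | 30% |

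The document gives neither q nor b, so every entry is an assumption.

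To put this in minutes: the intended addition per one-hour lesson is 4 + 3×2 = 10 minutes. If δ were that full 10 minutes, q = 20% and a change score would give 10 − 1×0.2×10 = 8 minutes.

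**The case against.** A reader might infer that intervention schools measured in September definitely knew their arm, that their readings were already treated, and that the claim of disclosure after baseline is false. The documents do not support that. Earlier disclosure is inferred from one sentence about training invitations, while the Randomisation section, the Fig. 2 note and the Blinding section all say the opposite. The text does not settle which side is loosely worded. The sentence on autumn training also makes it plausible that some September visits preceded delivery, though it concerns teachers' availability and does not establish the order.

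The Data analysis plan does not say that baseline VPA enters the model. It names a baseline measure of the outcome only for maths. Without baseline adjustment there is no shrinkage. The weights of 0.5 and 0.7 have no source in the article. The slope could be lower, because each school is visited once at each time point and results are summarised as class averages. The table also assumes the full effect is present at the visit, so for any given q and b a partial effect would give less.

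Delivery can be judged from the March–May 2018 comparison between arms alone, which randomisation supports without a baseline. A bias towards no effect would not create a false positive. The article also states the September dates openly.

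All of this stands, and it limits the size and certainty of the harm. It does not remove the conflict between the dates and the stated protection. Nor is this a detail left to an analysis plan, because the article itself fixes the window and calls it baseline.

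**Conclusion.** The article's statements on timing conflict. For intervention schools visited in September 2017, the VPA reading is not assured to precede either disclosure or delivery. The number and arm of these schools, and the order of visit and first lesson, are not given.

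The likely consequence is a bias of the VPA effect towards zero, conditional on baseline being used. Under the assumptions above it ranges from nothing (b = 0) to 30% (q = 30%, change score). The issue is confined to accelerometer-measured VPA. The primary maths outcome, whose baseline is the Key Stage 2 score, is untouched. This should be fixed, but it does not threaten the trial's main conclusion.

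**What to change.** 1. Reconcile the Design, Randomisation, Intervention, Blinding and physical-activity sections and the Fig. 2 note, so that they say when each school was told its arm relative to its accelerometer visit.
2. Report how many schools were measured in September 2017, by arm and, for intervention schools, by timing relative to training and first delivery. The visit dates should settle how far the concern applies.
3. In any VPA analysis that uses baseline, do not treat September 2017 readings as pre-intervention. Apply one calendar-date rule to both arms: set those readings to missing and keep the school in the model, for example with mean imputation plus a missing-baseline indicator, or with a longitudinal model that constrains the arms to a common baseline mean. A rule tied to training or delivery dates would discard less, but it has no counterpart in control schools.
4. At the least, add a sensitivity analysis limited to schools measured in May–July 2017, and an analysis of the March–May 2018 values without baseline adjustment.

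No new data are needed, and the article reports that secondary data collection was still underway, so the rule can be set before analysis. The cost is a few lines of text, one or two extra models and slight loss of precision, including some control-school readings that the intervention could not have affected. The May–July restriction selects schools on a feature that arose after randomisation, so it should remain a sensitivity analysis.

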##### Covariates

Information about pupils’ ethnicity and language proficiency is collected as part of the online assessments.

##### Brain imaging sub-study

A sub-sample of participants is being recruited to participate in additional testing to investigate the effect of the physical activity intervention on brain structure and function.

The brain imaging sub-study runs in parallel with the main trial, making optimal use of the intervention. Assessments will take place pre-intervention (baseline), immediately post-intervention (t1) and 12 months post-intervention (t2). The brain imaging sub-study consists of two sub-samples, recruited at different times during the trial:The first cohort of 60 participants completed brain-study assessments pre-intervention, and will complete identical assessments post-intervention to investigate pre-to-post intervention changes. Participants will also be invited to complete a set of assessments 1 year following the intervention.A second cohort of 50 participants will be recruited for post-intervention assessments that are similar, but not identical, to the assessments of the first cohort, as well as 1-year follow-up assessments. The addition of this cohort will enable cross-sectional analysis of between-group differences in a second sample.

Figure 3 shows a diagram of the participant flow, for each cohort, through the study. Details of recruitment for the brain imaging sub-study as well as an overview of assessments per cohort are provided in Additional file 2.

**Fig. 3 Fig3:**
[figure not shown]
Flow diagram brain imaging sub-study. ^1^Note: post-intervention assessments differ between cohorts 1 and 2, but not within a cohort; see text and Additional file 2: Figure S7. Abbreviations: *MRI* magnetic resonance imaging, *n* number of schools, *nS* number of subjects, *PE* physical education, *VO*_*2*_*max* maximal oxygen consumption, *VPA* vigorous physical activity

The sub-study has been granted separate ethical approval by the University of Oxford Medical Sciences Inter-Divisional Research Ethics Committee (Registration No. R51313) and was retrospectively registered (19 July 2018) at ClinicalTrials.gov (ID NCT03593863).

##### (a) Brain imaging sub-study outcome measures

Magnetic resonance imaging (MRI)

Scanning is carried out at the Wellcome Centre for Integrative Neuroimaging, Oxford, using a 3T Siemens Magnetom Prisma (Erlangen, Germany) scanner with a 32-channel head coil. The MRI protocol comprises both functional and structural sequences, takes approximately 55 min to complete and includes (1) T1-weighted (T1w) structural MRI, (2) resting-state functional MRI (rs-fMRI), (3) diffusion-weighted MRI (DW-MRI), (4) quantitative fast low angle shot (FLASH) MRI, (5) pseudo-continuous arterial spin labelling (pCASL) and (6) MR angiography (MRA; at post-intervention only). Full details of the MRI protocol are provided in Additional file 2.2.Cognitive measures

Cognitive performance is assessed using tests of visual short-term memory (object-location task [69–71]), relational memory (relational memory task [10]), cognitive flexibility (colour-shape switch task [46]) and planning (Tower of London task [72–74]). Details of the cognitive assessments are provided in Additional file 2. The tests are completed in the lab at baseline (cohort 1), post-intervention (cohorts 1 and 2) and follow-up (cohorts 1 and 2). Cohort 1 completes tests of visual short-term memory and mental associations as well as relational memory and cognitive flexibility. The latter tasks are taken from the main trial and repeated in the brain imaging sub-study to (a) obtain a well-controlled, lab-based measure of the task for cross-validation, and (b) ensure that all brain-study participants will have a score on this task, independent from their main trial completion. Cohort 2 completes tests of visual short-term memory and planning.3.Mental and physical health measures

A comprehensive set of online questionnaires is completed by all participants at baseline (cohort 1), post-intervention (cohorts 1 and 2) and follow-up (cohorts 1 and 2).*Attention-deficit hyperactivity disorder (ADHD)* symptoms are assessed by the ADHD rating scale IV [75], completed by a parent of the participant.*Puberty status* is assessed using the Pubertal Development Rating Scale [76], a self-report measure of physical development for youths under the age of 16.*Mood* is assessed using the abbreviated Profile of Mood States (POMS) [77]. The abbreviated POMS scale is a well-validated questionnaire that contains 40 self-report items on a 5-point Likert scale.*Sleep* is assessed using the Cleveland Adolescent Sleepiness Questionnaire (CASQ [78] and the Sleep Condition Indicator (SCI) [79]. The CASQ is a self-report scale to measure excessive daytime sleepiness. The SCI is an 8-item self-report measure of insomnia symptoms, based on Diagnostic and Statistical Manual of Mental Disorders, 5^th^ edition (DSM-5) criteria, and it captures both sleep problems and daytime functions.*Mental health* is assessed with the SDQ [49].*General health and behaviour* are assessed using various items of the HBSC survey (2009/2010) [80], capturing body image, eating behaviour, oral health, physical activity, leisure time activity, substance use, family structure, peer relationships, self-rated health and socio-economic environment.4.Psychological variables linked with daily MVPA.

The study also includes exploratory explicit and implicit measures of psychological variables linked to daily average PA, using the frameworks set out in the Theory of Planned Behaviour [63, 64] and the Prototype Willingness Model [65]. Additional details are provided in Additional file 2.5.Physical activity, fitness and gaitPhysical activity

Daily average MVPA during a typical week in school term is measured using the Axivity AX3 accelerometer. A 7-day protocol (5 weekdays and 2 weekend days) is sufficient to obtain a reliability coefficient of 0.8 or above when assessing adolescent PA [81].(b)Cardiorespiratory fitness

Cardiorespiratory fitness is measured using a standard maximal oxygen consumption (VO_2_max) incremental step test, in which the rate of oxygen consumption is measured while the participant cycles on an ergometer. Resistance is increased every minute until the participant reaches volitional exhaustion or is unable to maintain a cadence of 60 revolutions per minute (rpm). Additional details are provided in Additional file 2.(c)Gait

Participants walk over a 10-m obstacle-free and flat surface walkway, while wearing a single inertial measurement unit (IMU, LPMS-B, Life Performance Research, Tokyo, Japan), to obtain temporal and spatial gait parameters [82, 83]. Participants perform two consecutive 10-m walks, taking approximately 20 s to complete.

